### Statistical Methods

#### Statistical Methods for Primary and Secondary Outcomes

In order to compare groups practicing in constant and variable practice conditions in terms of brain’s structural and functional changes, repeated measures ANOVA with time as a within-participants factor, and practice condition as a between participants factor, with *post-hoc* tests will be used. The relationship between MRI brain changes and motor task proficiency will be evaluated using partial correlations.

Frequency analysis will be performed separately for each EEG channel and trial using fast Fourier transform (FFT). Significant differences against baseline will then be compared between participant groups. Connectivity analysis will be performed using the calculation of coherence (Nunez et al., 1997, 1999) between channels of interest. Results will be statistically compared between participant groups. Because of the multiple usages of statistical tests, multiple comparison corrections will be used.

Motor task proficiency will be assessed using parametrical or non-parametrical tests, depending on the results of the assumption tests (homogeneity, normality). The possible tests include but are not limited to correlations, t-test, and analysis of variance (2 × 3 model; two practice conditions × three time points) with the following *post-hoc* analysis for all significant main effects.

We may use Bayesian equivalents of the tests mentioned above.

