### Outcomes

Primary Outcome Measure:

1. Brain structural and functional changes following constant and variable practice conditions in motor learning (structural, diffusion, and resting-state fMRI):

Structural, diffusion, and resting-state functional scans will be acquired both prior to and after the 3 weeks of practicing the unimanual index finger abduction motor task. High-resolution T1-weighted (MPRAGE) and FLAIR images will be exploited to assess gray matter changes. Diffusion-weighted (DWI) data will be used for probabilistic tractography to obtain specific tracts that will be analyzed in terms of alterations in fractional anisotropy, mean, radial, and parallel diffusivity. In addition, whole-brain white matter microstructural changes will be assessed using Tract-Based Spatial Statistics (TBSS).

Regarding resting-state fMRI data, BOLD multi-echo echo-planar imaging fMRI sequence will also be performed. In addition to resting-state functional connectivity (rs-FC) analysis among regions of interest, an Independent Component Analysis will also be used to evaluate rs-FC changes of large-scale brain networks of interest.

2. EEG brain waves characteristics and motor task proficiency outcomes (estimated from simultaneous EEG and force recordings during motor task performance, i.e., UIFA) differences in constant and variable practice conditions in motor learning and as a function of practice time:

To record bioelectrical signals from the brain cortex (EEG) during the performance of unimanual index finger abduction (UIFA) motor tasks, we will use the scalp 256-channel EEG data acquisition system (Electrical Geodesics, Inc., Eugen, OR, USA) with sponge electrodes (the “wet” EEG system by Electrical Geodesics, Inc. Eugen, OR, USA). The force induced during the UIFA will be recorded and visualized for participants (as feedback) using the same custom-made system as described in the Section “Intervention Description”. Also, during the UIFA performance, the same force signal will be sent synchronously to the EEG acquisition system (Electrical Geodesics, Inc., Eugen, OR, USA), and will be recorded simultaneously. The force signals will be used as triggers for subsequent EEG analysis.

Two types of UIFA motor paradigms will be used during simultaneous EEG and force recordings in pre- post-, and retention tests, i.e., (1) the UIFA SPSIC paradigm (SPSIC—step isometric contractions) and (2) UIFA MRCP paradigm (MRCP—motor-related cortical potential).

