Both groups will perform 40 MRCP trials, i.e., 10 s radial abduction to 20% MVC of UIFA task and 10 s rest. The MRCP will provide a reliable time-domain estimation of the amplitude, latency, source, and connectivity analysis. The EEG signals recorded during the MRCP paradigm will be analyzed using: (1) averaging technique to assess an amplitude of MRCP showing the level electrical activity of cortical regions engaged during motor task performance, (2) EEG source analysis, showing current dipole of activation as a model of the electrical current, that characterizes of location, orientation and strength or amplitude [expressed in dipole moment (nAm)], which describes the directional activity of brain region engaged in a motor task, and (3) time-frequency and connectivity analysis, to explore the strength of functional coupling between cortical regions responsible in motor preparation and execution. We will analyze the EEG data in co-registration with individual T1 structural MRI scans in the Talairach space, a 3-dimensional human brain coordinate system used to map the location of brain structures independent from individual differences in the size and overall shape of the brain.

UIFA motor task proficiency outcomes for the UIFA SPSIC and UIFA MRCP will be obtained based on the force signal processing and analyses in the time domain. We will estimate a motor performance accuracy based on the error percentage of achieved force level in reference to the given target force level while performing the various sequences of SPSIC-UIFA motor tasks. Also, we will assess the speed of force generation by estimating the time and rate of force development during the execution of the various sequences of SPSIC-UIFA motor tasks.

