### Sample Size

In order to calculate the sample size, we used mean and standard deviation (SD) values (Dean et al., 2013) presented by Cheng and colleagues in Table 1, specifically, values for Time Window 1 (T1) for novice and expert participants (Cheng et al., 2015). We set confidence interval = 95%; power = 0.8; ratio of sample size = 1 (constant practice group vs. variable practice group). As a result, a minimal sample size estimated was eight participants in total, four participants per group. Given, we were going to recruit novices for both groups, the possible drop-out, statistical requirements (e.g., at least five observations perc variable in regression models), and considering potential recording problems, we decided to measure 25 participants per group.

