### Assignment of Interventions: Allocation

#### Sequence Generation, Concealment Mechanism, and Implementation

All participants will be randomly assigned to the constant and variable practice condition groups (CG and VG, respectively) with a 1:1 allocation ratio. An online randomization generator^1^ with three blocks of four, three blocks of six, and two blocks of 10 participants will be used.

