### Data Collection and Management

#### Plans for Assessment and Collection of Outcomes

Pretest, posttest, and retention tests will consist of MRI, EEG, and motor task proficiency assessments.

Changes in the gray matter will be estimated using voxel-based morphometry (Ashburner and Friston, 2000), which constitutes the whole-brain gray matter probabilities comparison. In addition, volumetric analyses will be calculated on both cortical and subcortical structures, and cortical thickness can be evaluated (Fischl et al., 2002). Variations in white matter microstructure can be assessed using Tract-Based Spatial Statistics (TBSS; Smith et al., 2006)—a method that applies voxel-wise statistics on diffusion metrics using projection onto an alignment-invariant tract representation. Representations of specific tracts can be obtained with probabilistic tractography (Behrens et al., 2007) that takes into account crossing fibers in individual voxels. The BOLD multi-echo echo-planar imaging (ME EPI) fMRI sequence will be applied regarding resting-state fMRI data. Representative time-series within chosen regions of interest (ROIs), i.e., dorsolateral prefrontal cortex, posterior parietal cortex, posterior parietal cortex, primary motor cortex, anterior cingulate cortex, cerebellar cortex, cerebellar dentate, putamen, thalamus primary, and motor cortex, will be extracted and used for seed-based analysis computation. Moreover, Independent Component Analysis (ICA) will be calculated in order to evaluate changes in large-scale brain networks’ connectivity, with the emphasis on fronto-parietal control network, dorsal attentional network, basal ganglia network, and sensorimotor network.

In order to test the sensorimotor cortex activity in constant and variable practice conditions, we decided to record the sensorimotor rhythm (SMR), which oscillates between 12 and 15 Hz in the motor cortex. SMR is widely used to indicate the activity of the sensorimotor cortex (Egner and Gruzelier, 2001, 2003) since there is a positive relationship between SMR power and inhibition of sensorimotor cortex activity.

Motor task proficiency will be measured as efficiency in repeating patterns of step isometric contractions (SPSIC) during UIFA using custom-made equipment.

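### The primary MRI group comparison uses the pretest only as an ANOVA time level; adjusting for it as a covariate would be more precise unless the measure is very stable

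*Protocol article*

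**What the plan says.** In Statistical Methods for Primary and Secondary Outcomes, the groups are compared on structural and functional brain change with "repeated measures ANOVA with time as a within-participants factor, and practice condition as a between participants factor", followed by post-hoc tests. No covariate is named for this comparison.

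The pretest is collected. Under Outcomes, structural, diffusion and "resting-state functional scans will be acquired both prior to and after the 3 weeks of practicing" the motor task. Plans for Assessment and Collection of Outcomes adds a third occasion: "Pretest, posttest, and retention tests will consist of MRI, EEG, and motor task proficiency assessments". Table 1 also marks MRI at retention.

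Allocation is random "with a 1:1 allocation ratio", and on sample size "we decided to measure 25 participants per group".

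For EEG, the same statistical section says of the frequency analysis that "Significant differences against baseline will then be compared between participant groups", and of coherence that "Results will be statistically compared between participant groups". Under Outcomes, the MRCP task is common to the arms: "Both groups will perform 40 MRCP trials, i.e., 10 s radial abduction to 20% MVC of UIFA task and 10 s rest". The SPSIC test is not: the variable group performs three patterns 15 times each, the constant group one pattern 45 times.

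**The concern.** Because participants are randomised, any pretest difference between the arms on a measure with the same content in both is due to chance. A group-by-time test subtracts the whole pretest value and so carries all of its noise. Using the pretest as a covariate subtracts only the part that predicts the post value. The group difference being estimated is the same, so the choice affects precision and not what is estimated.

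What is at stake is power. The recruited number is 25 per group. Participants with missing tests or training sessions are excluded, so the analysed number can only be lower, and the planned multiplicity corrections reduce power further. The article's Sample Size section starts from a novice-expert contrast and gives the recruitment of novices in both groups as one reason for enlarging the sample. A smaller true difference than the one behind the calculation is therefore plausible.

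**Working it through.** **The plan's own figure.** Sample Size reports a minimum of 8 in total (4 per group), then raises this by judgement to 25 per group. The means and SDs used are not in the article, so the figure cannot be reproduced. Solved backwards (normal approximation, two-sided 0.05, 80% power), 4 per group corresponds to a difference of about 1.98 to 2.29 SD. Nothing below depends on it.

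**Inputs.** n = 25 per group and 1:1 allocation (article); two-sided alpha 0.05 (assumed from the stated 95% confidence); equal SDs at pretest and posttest (assumed). Rho is not given, so 0.3 to 0.95 is shown. Effects are in posttest SD units.

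**Variance factors for the group difference, one posttest**
- Group-by-time interaction (identical to a change-score t-test, 48 df): 2(1-rho).
- Post value adjusted for pretest (ANCOVA, 47 df): 1-rho².
- Large-sample ratio: (1-rho²)/[2(1-rho)] = (1+rho)/2.
- Finite-sample cost of chance pretest imbalance, with N = 50: 1 + 1/(N-4) = 1 + 1/46 = 1.022, about 2%.
- Ratio at this sample size: 1.022 × (1+rho)/2. It reaches 1 when rho = 2 × 46/47 - 1 = 0.957.

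**Power at the effect where the interaction has 80%.** The last column averages ANCOVA power over the distribution of chance pretest imbalance. Simulation agrees to within about 0.3 points.

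| rho | effect (SD) | (1+rho)/2 | ratio with 2% cost | ANCOVA power, large-sample formula | ANCOVA power, finite sample |
|---|---|---|---|---|---|
| 0.3 | 0.957 | 0.65 | 0.66 | 93.5% | 93% |
| 0.5 | 0.809 | 0.75 | 0.77 | 89.9% | 89% |
| 0.7 | 0.626 | 0.85 | 0.87 | 85.9% | 85% |
| 0.9 | 0.362 | 0.95 | 0.97 | 81.9% | 81% |
| 0.95 | 0.256 | 0.975 | 1.00 | 81.0% | 80% |

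For an assumed 0.6 SD difference at rho 0.5, power is 55% with the interaction and about 66% with adjustment (67% by the large-sample formula).

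**If MRI is also acquired at retention.** This was simulated with equal correlations of 0.5 between all occasions, 0.6 SD at both follow-ups and 3,000 runs.
- Two-df interaction: 56%.
- ANOVA group main effect: 39%. It is diluted because it averages in a pretest where randomisation allows no true group effect.
- One-df change contrast, mean of the two follow-ups minus pretest: 66%.
- Pretest-adjusted mean of the two follow-ups: 83%.

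The step from 56% to 66% comes from a focused contrast. Only the step from 66% to 83% comes from the covariate.

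**The case against.** The strongest reply is that nothing in the section is false. A group-by-time ANOVA is a standard, unbiased analysis and it does use the pretest. This stands: the issue is efficiency only. A reader might infer that the ANOVA is biased or ignores the baseline, but the article does not support either reading.

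Second, the objectives ask for brain changes following practice, and the rationale for three weeks of training expects structural change in both groups. A model of post values adjusted for pretest does not estimate that time effect. This also stands, and is why the ANOVA should be kept for it.

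Third, the gain depends on a correlation the article does not give. For highly reproducible measures, possibly brain volumes, it is negligible, and above about rho 0.957 adjustment is slightly worse at this sample size. So it cannot be said that adjustment is never less precise. The range is shown for that reason.

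Fourth, a reader might infer that EEG coherence is compared on post values alone, because the sentence on it names no pretest term. The article does not say so. It frames the EEG outcome as a function of practice time, and such detail may properly sit in an analysis plan that is not shown. Coherence is not part of this point. The MRI point does not rest on silence, since its model is stated.

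**Conclusion.** The point holds as a recommendation on efficiency for the primary MRI outcomes. The stated group-by-time test is valid but, for measures of low to moderate reproducibility, less precise than a pretest-adjusted comparison of the same data. With pre and post levels and 25 per group, 80% power becomes about 93% at rho 0.3, 89% at 0.5, 85% at 0.7 and 81% at 0.9, with no gain from about 0.95. These figures assume equal SDs, two-sided alpha 0.05 and complete data on all 50 participants. No rho is documented for any outcome, so how much each MRI measure would gain cannot be settled from the article.

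**What to change.** In Statistical Methods for Primary and Secondary Outcomes, define the primary between-group MRI contrast as the group difference in post-practice values (posttest, and retention where acquired), adjusted for the participant's own pretest value. Use ANCOVA for one post-practice occasion. For two, use a mixed model with group, time, group-by-time, pretest and pretest-by-time, and say which time point or average carries the primary contrast. For region-of-interest or voxel-wise analyses, enter the pretest value or map as the covariate. Keep the repeated-measures ANOVA for the time effect, that is, change following practice.

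The same adjustment can be used for the MRCP EEG measures, whose task is the same in both arms. It should not be used with the SPSIC pretest, whose content differs by arm.

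The cost is a change of wording, one degree of freedom per model for a single post-practice occasion, and somewhat more set-up for voxel-wise covariates. No further data are needed.

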There have been no previous studies on cortical networking in constant and variable practice and motor learning; we decided to assess such communication measuring EEG coherence (Deeny et al., 2009). A significant linear relationship exists between time series simultaneously recorded from two locations (high coherence), indicating communication between these areas of the cerebral cortex. In contrast, low coherence indicates the opposite (Deeny et al., 2009). We may expect decreased coherence between premotor (Fz) and motor (C3, C4) areas of the cortex and between the premotor and occipital regions as the practice of a visuo-motor task progresses (Busk and Galbraith, 1975). However, if the constant and variable practice condition groups receive the same amount of practice, we may expect that pairing electrodes in specific regions will be undifferentiated (Deeny et al., 2003). Lelis-Torres and colleagues (Lelis-Torres et al., 2017) noted that when investigating the cognitive effort involved in random compared to constant practice schedules, the random practice induced significantly greater cognitive effort than constant practice. Throughout the practice, both task engagement and mental workload decreased more in the constant practice condition than in the random practice condition. However, the random schedule is only one variant of variable practice. Another extreme is the blocked practice schedule. Variable practice in blocked order assumes that a learner is practicing many skill variations but in blocks (or time). Although, authors agree that this is also variable practice (Van Rossum, 1987; Czyż, 2021), some doubt whether this variability differs from constant practice (Kim et al., 2021b). This ambiguity will be tested in our study.

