The participants from VG will perform three types of SPSICs (1–3), each repeated 15 times (together 45 trials), but the participants from CG will perform 45 times of one type of SPSIC. This SPSICs will be analyzed in the frequency domain using force signal as a trigger for extracting SPSIC sequences related to time frames of EEG time series data. We will estimate EEG signal’s power spectrum density (PSD) for sensorimotor rhythm (SMR, frequency band 12–15 Hz) as well as for other frequency bands: delta (0.5–4 Hz), theta (4–8 Hz), alpha (8–14 Hz), beta (14–35 Hz) and gamma (35–70 Hz). PSD-EEG analysis will reveal the level of the electrical activity of cortical regions engaged during UIFA motor tasks performance under the constant and variable practice conditions. We will also estimate coherence between EEG signals (EEG-EEG coherence) from electrodes in a chosen region of interest based on the PSD-EEG analysis. Analysis of EEG-EEG coherence calculates the linear relationship between the power spectra of two EEG signals taken from two EEG electrodes placed on the scalp. A significant linear relationship existing between time series simultaneously recorded from two locations (high coherence) indicates a high level of functional communication (connectivity) between these areas of the cerebral cortex, whereas low coherence indicates the opposite.

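### EEG power results pass a significance-against-baseline filter and coherence regions are picked from the same recordings, with no group-blind rule stated for either step

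*Protocol article*

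**What the plan says.** EEG during the motor task is part of the second primary outcome. Under Statistical Methods for Primary and Secondary Outcomes, spectra are computed by channel and trial, and then "Significant differences against baseline will then be compared between participant groups". That is the only route from EEG power to a group comparison in that section. The repeated measures ANOVA with time and practice condition, described just before it, is worded for structural and functional brain changes, which is how the Outcomes section words the MRI outcome.

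Under Outcomes, EEG-EEG coherence is to be estimated "from electrodes in a chosen region of interest based on the PSD-EEG analysis". The statistical section then speaks of coherence "between channels of interest. Results will be statistically compared between participant groups" and does not list the channels. It promises multiple comparison corrections without naming the method or the family of tests.

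Background and Rationale does name connections of interest: "We may expect decreased coherence between premotor (Fz) and motor (C3, C4) areas of the cortex and between the premotor and occipital regions" as practice progresses. Neither the Outcomes section nor the statistical section uses them to fix the channels.

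**The concern.** The group question is whether change differs between constant and variable practice. Answering it needs a test of that difference in every participant's data. Screening first on significance against baseline changes what is compared. If the screen is run within each group, whether a channel survives depends partly on chance differences between the groups, and those same differences drive the later comparison.

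The coherence step has the same structure. If the region is chosen because power differs between groups there, and power and coherence are correlated, the coherence test starts from a region where the groups already differ by chance.

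At stake is the error rate of the EEG power and coherence comparisons, within a primary outcome. In the other direction, a filter requiring significance in both groups could discard channels where only one group changes, which are of direct interest here.

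**Working it through.** The plan gives no figure for this step, so there is none to reproduce.

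**Inputs from the protocol.** 25 participants per group (Sample Size). A 95% confidence level (Sample Size), taken as two-sided alpha 0.05. The recording system has 256 channels, and power is estimated in six bands (sensorimotor rhythm plus five), so 256 × 6 = 1,536 channel-band results. The bands overlap, so these are not independent, and the calculations below do not use that count.

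**Check 1: the baseline filter.** Each participant's change is drawn from a normal distribution with SD 1 and the same mean in both groups, so there is no true group difference (200,000 runs). Each group's change is tested against zero with a one-sample t-test (24 df) and the groups are compared with a two-sample t-test (48 df). If each group is significant with probability p, exactly one is significant with probability 2p(1 − p). For example, p = 0.30 gives 2 × 0.30 × 0.70 = 0.42.

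| Common change | p | Exactly one group significant | Group test rejects, given at least one significant | given both significant | given pooled change significant | no filter |
|---|---|---|---|---|---|---|
| 0 | 0.050 | 0.095 | 0.332 | too few | 0.056 | 0.050 |
| 0.2 | 0.161 | 0.270 | 0.142 | 0.024 | 0.055 | 0.050 |
| 0.3 | 0.300 | 0.419 | 0.092 | 0.005 | 0.053 | 0.050 |
| 0.4 | 0.485 | 0.500 | 0.067 | 0.007 | 0.051 | 0.050 |
| 0.5 | 0.668 | 0.442 | 0.056 | 0.012 | 0.051 | 0.050 |
| 0.6 | 0.821 | 0.295 | 0.051 | 0.018 | 0.050 | 0.050 |
| 0.8 | 0.969 | 0.058 | 0.050 | 0.037 | 0.050 | 0.050 |

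**Check 2: the coherence region.** There are K independent candidate regions, no true group difference in power or coherence, and a correlation rho between a participant's power change and coherence change (20,000 runs). The region with the largest absolute group t-statistic for power is chosen, and coherence is then tested there at 5%. K, rho, independence and this selection rule are all assumptions; the protocol gives none of them.

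| K | rho 0.3 | rho 0.5 | rho 0.7 |
|---|---|---|---|
| 5 | 0.068 | 0.096 | 0.146 |
| 10 | 0.079 | 0.126 | 0.205 |
| 20 | 0.085 | 0.159 | 0.278 |

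At rho = 0 the rejection rate is 0.048-0.050. Choosing the region on the power change pooled over both groups gives 0.049-0.052 throughout.

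**The case against.** A reader might infer that the plan declares a group difference wherever one group is significant and the other is not. The text does not say so. The sentence announces a comparison between groups, and it also fits a direct group test on contrasts that passed the filter. The 42-50% figures apply only if significance labels are compared in place of a test.

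A reader might also infer that the coherence selection is circular. That needs a choice that depends on group. The Outcomes section presents the power analysis as showing which cortical regions are active during the task, under both practice conditions, so choosing regions by task engagement is at least as natural a reading. That choice is harmless if it is made on pooled data. Baseline is also undefined. It could be the pretest or rest within a trial, and a pooled filter on task-responsive channels would be close to nominal.

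The filter only removes tests, so false rejections counted over all channels do not exceed 5%. At a common change of 0, at least one group passes with probability 1 − 0.95² = 0.0975, and 0.0975 × 0.332 = 0.032. A correction counted over every channel screened, or every candidate region, would therefore hold. A correction counted only over the tests that survive would not, and the protocol does not say which is meant.

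The coherence results are separately said to be compared between groups. An itemised channel list is commonly left to an analysis plan.

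These points limit the claim but do not remove it. The filter is a stated step, not an omitted detail, and no passage makes either selection group-blind.

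**Conclusion.** The point stands in conditional form. The protocol writes its EEG power comparison as a significance filter followed by a group comparison, and chooses coherence regions from the same recordings. Some readings that the text permits misstate the error rate. With a filter on significance in at least one group, the conditional type I error is about 0.33, 0.14 and 0.09 at common changes of 0, 0.2 and 0.3, and close to 0.05 from 0.6 up. With a filter on both groups it is 0.005-0.037 at changes of 0.2-0.8. With a region picked on the group contrast in power, the coherence test rejects about 8-28%, given 10-20 independent candidates and a correlation of 0.3-0.7. Other permitted readings, pooled over groups, are sound.

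This does not show that the group comparisons are invalid, and it does not extend to the amplitude and source analyses of the motor-related cortical potential paradigm, which neither sentence covers. It is a cheap improvement to a stated method in a primary outcome, worth making before the data are analysed.

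**What to change.** In the statistical section, drop the significance filter. Test the between-group difference in change (group by time) directly, whatever the within-group results. Do this for sensorimotor rhythm power over the motor cortex, where Plans for Assessment and Collection of Outcomes already places it. For the other bands, use prespecified channels or one whole-scalp cluster-based permutation test of the group contrast.

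In the Outcomes and statistical sections, either fix the coherence channels before the data are seen, or choose them from the task effect pooled over groups by someone blind to allocation. The connections in Background and Rationale (Fz with C3 and C4, premotor with occipital) are one candidate set. However, that section predicts a change with practice there and, given equal practice, expects electrode pairings not to differ between groups. The sponsor should therefore decide whether those are the connections on which to centre a group test.

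The cost is mainly wording, plus that decision. Effects in unexpected regions become exploratory.

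### Motor proficiency, part of a primary outcome, has no fixed deciding comparison: assumption tests choose the analysis from an open-ended list whose tests answer different questions

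*Protocol article*

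**What the plan says.** The Outcomes section lists as the second primary outcome "EEG brain waves characteristics and motor task proficiency outcomes", compared between practice conditions and as a function of practice time. It describes three motor measures: the percentage error of achieved against target force, the time of force development, and the rate of force development.

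The analysis is set under Statistical Methods for Primary and Secondary Outcomes:

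- The choice of test: "Motor task proficiency will be assessed using parametrical or non-parametrical tests, depending on the results of the assumption tests (homogeneity, normality".
- The menu: "The possible tests include but are not limited to correlations, t-test, and analysis of variance". The ANOVA is described as two practice conditions by three time points, with post-hoc analysis promised for significant main effects.
- A further option: "We may use Bayesian equivalents of the tests mentioned above". No trigger or decision threshold is attached.

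A sentence promising multiple comparison corrections closes the preceding paragraph, which is about EEG. It names neither a method nor a family of tests.

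**The concern.** The items on the menu answer different questions. The outcome is a group difference as a function of practice time, which is a group-by-time question. The interaction term of the 2 × 3 ANOVA addresses it. A t-test at post or retention compares groups at one time. The usual two-sample rank tests also compare groups on one variable and carry no interaction term. Post-hoc work is tied to main effects, and a main effect of time would be expected if both groups simply learn, which says nothing about constant versus variable practice. So an assumption test may change the hypothesis as well as the method of computing a p-value.

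With three measures, more than one post-training time point and several ANOVA terms, a significant result from any of several analyses could be presented as the planned one. The Blinding section says the researchers are not blinded, so the choice could be made by people who know the allocation.

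**Working it through.** **Inputs.** 25 per group (Sample Size); three time points (Statistical Methods). No significance level is stated for this outcome. The nearest statement is "We set confidence interval = 95%; power = 0.8; ratio of sample size = 1", so two-sided 5% is assumed. The plan gives no false-positive rate here, so there is no figure of its own to reproduce. Within-person correlation and distribution are not given and are assumptions below.

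**Step 1: independent looks.** With k independent tests at 5%, the chance of at least one false positive is 1 − 0.95^k:

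- k = 2: 1 − 0.9025 = 9.8%
- k = 3: 1 − 0.8574 = 14.3%
- k = 4: 1 − 0.8145 = 18.5%

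Real contrasts on the same participants are correlated, so simulation is needed.

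**Step 2: simulation with no true effect.** 25 per group, three time points, one measure, 2,000 runs per scenario. Scenarios: normal data with within-person correlation 0.5 and 0.8, and lognormal data with 0.5. The Monte Carlo standard error is √(0.05 × 0.95/2000) = 0.5 points near 5% and √(0.2 × 0.8/2000) = 0.9 points near 20%.

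| What counts as success | False-positive rate |
|---|---|
| Pre-named group-by-time interaction | 4.6–5.2% |
| One contrast; Shapiro-Wilk and Levene choose t or Mann-Whitney | 4.2–5.0% |
| One contrast; better of t and Mann-Whitney | 5.6–5.8% |
| Post or retention, each gated | 7.6–9.4% |
| ANOVA group or interaction term | 9.1–9.9% |
| Gated post and retention, plus ANOVA group and interaction | 12.7–13.8% |
| Gated post, retention and both change scores | 13.9–16.9% |
| All of these, t or rank version of each | 18.7–20.3% |

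A second simulation used correlations 0.3, 0.5 and 0.8 and 2,500 runs. The interaction or a t-test at post or retention gave 11.0–13.3%; adding the group effect and Mann-Whitney tests gave 13.8–17.0%. A further run of the gate on one contrast gave 4.8–6.2%, again about 5%.

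**Step 3: how often the gate would fire.** If normality is tested in each of the six group-by-time cells, chance alone rejects at least one in 1 − 0.95^6 = 26.5% of trials with perfectly normal data (simulated 25–27%). This describes how often chance would pick the test. It is not a false-positive rate for the treatment comparison, as the second row of the table shows.

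**Step 4: what a fixed pretest-adjusted comparison offers.** Assume a 0.6 SD group difference at retention. Approximate power is Φ(0.6 / (√(2/25) × √(1 − ρ²)) − 1.96), with ρ = 0 for the unadjusted t-test.

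- Unadjusted: 0.6/0.283 = 2.12, power 56%
- Adjusted, ρ = 0.5: 2.12/0.866 = 2.45, power 69%
- Adjusted, ρ = 0.8: 2.12/0.6 = 3.54, power 94%

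Simulation gave slightly lower or equal values: 53% rising to 64% at ρ = 0.5, and 54% rising to 94% at ρ = 0.8, with type I error about 5%.

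**The case against.** The strongest objection is to the number. A reader might infer that picking the test from assumption tests makes the false-positive rate about three times 5%. The document does not support that. The gate on one contrast stays near 5%, and taking the better of t and rank test adds less than one point. A threefold rate needs several analyses, success on any one, and no correction, and the protocol states no such decision rule. The protocol does promise multiple comparison corrections. If that sentence covers motor proficiency and is applied effectively, the rate returns towards 5%. All of this stands, and the figures are conditional for that reason.

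It is also tempting to say that force error and timing data are skewed, so the switch to rank tests is nearly certain. The protocol gives no distributional information, and each test session has 45 step-contraction trials, so participant averages may be less skewed than single trials. Nor does it name any rank test: one applied to change scores would still address group by time. The loss of the interaction is therefore a possibility that the wording allows.

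Finally, this is a condensed article, the analysis plan is not shown, and motor proficiency is absent from the Objectives section. That lowers the stakes, but it does not dispose of the point. The text states a data-dependent, open-ended rule for something that it lists as primary, and a later plan could adopt almost any test and still comply. The same section fixes a repeated measures ANOVA for the MRI outcomes without any gate, so the article was able to be specific.

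**Conclusion.** The point holds in a limited form. Statistical Methods fixes no measure, time point or contrast as decisive for motor proficiency, and it lets pretests on the trial's data choose among analyses of different hypotheses, with optional Bayesian versions. The false-positive rate is near 5% if one contrast is fixed, gate or no gate. It is about 12–18% if several contrasts and tests are tried on one measure with any one sufficing and no correction, and up to about 20% with more contrasts. These figures assume two-sided 5%, 25 per group, and the correlations and distributions stated above. Choosing among the three measures would add to them. The Bayesian option cannot be quantified because no threshold is given. The inflation should be attributed to free choice of measure, time point and contrast, and not to assumption testing as such.

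**What to change.** In Statistical Methods, replace the gate and the open list with one analysis that does not depend on an assumption test:

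1. Name one motor measure, for example percentage force error.
2. Name one time point or contrast.
3. Estimate the group difference adjusted for the pretest value, by ANCOVA or the equivalent mixed model, with a robust or permutation p-value. This removes the reason for a normality gate without assuming a transformation.
4. Delete the wording that leaves the list of tests open.
5. Label the other measures, rank tests and Bayesian versions as secondary or sensitivity analyses that cannot change the conclusion.

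The sponsor should also state whether the multiplicity sentence in the EEG paragraph applies to motor proficiency. The cost is a wording change before analysis and a little programming; no participant procedure changes. The downside is that analysts give up the freedom to choose the test later.
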